**Studyproposal**

**Titel:**

**The impact of visceral osteopathic treatment on the meconium evacuation in very low birth weight infants**

**Masterthesis Osteopathy by Doz. [name]**

**at the Donauuniversity Krems**

**Introduction:**

The physiologic immaturity of the intestinal motor mechanisms and the associated feeding problems are one of the challenges for neonatologists in the treatment of very low birth weight infants (VLBW- infants= with a birthweight <1500gram). Timing of the first and last meconium stool is critical for oral feeding tolerance and proper gastrointestinal function [1]. The vast majority of term infants (99.8%) pass their first meconium within 48 hours of life [2], while premature infants show a wide variability. The time to pass their first meconium ranges from 1 hour to 27 days (median: 43 hours) ([3, 4]. Obstruction of the gastrointestinal tract by tenacious, sticky meconium frequently leads to gastric residuals, a distended abdomen and delayed food passage. Recent data support the concept that complete rapid evacuation of meconium plays a key role in feeding tolerance [5]. Duration to full enteral feedings is extended, the probability to acquire infections due to intravenous access for parenteral nutrition increases and hospital stay of the infant prolongates. Data from a study including 21 preterm infants with the diagnosis “Meconium obstruction in the very low birth weight premature infant” showed that tenacious meconium is most frequently located in the distal ileum [6]. In that study, various kinds of enemas were demonstrated to be effective and safe for promoting the evacuation of tenacious meconium plugs during or shortly after instillation. Resolution of obstruction with glycerin suppositories, saline, acetylcystein or non-absorbable contrast media was conducted in 70% of symptomatic infants, thereby avoiding surgical removal of the plug. Recently, the study group around Haiden et al performed a prospective randomized trial; to determine whether repeated prophylactic applications of small volume glycerin enemas are effective in accelerating passage of meconium in VLBW infants [7]. The authors did not find a correlation between application of enemas and meconium evacuation. A reason for the ineffectiveness of glycerin enemas was supposed to be that the volume used was too small to mobilize tenacious meconium sufficiently from deep parts of the colon and small bowel (Colon ascendes, terminal Ileum).

**Osteopathy**

Osteopathy is a complete system of medical care with a philosophy that combines the needs of the patient with current practice of medicine, surgery and obstetrics, that emphasizes the interrelationship between structure and function and that has an appreciation of the body’s ability to heal itself[8]. Osteopathy has been considered a form of complementary medicine, emphasizing a holistic approach and the skilled use of a range of manual and physical treatment Techniques and methods which are non- invasive, and conducted by exclusively using the osteopaths hands as a diagnostic and treatment tool.

Techniques of osteopathic treatment[9]:

Cranial osteopathy: Cranial osteopathy is a set of theory and techniques that have been developed from the observations of [[name]](http://en.wikipedia.org/wiki/William_Garner_Sutherland) that the plates of the cranium permit microscopic movement or force dissipation and that there is a 'force' or rhythm that is operating in moving the plates of the skull.[10] Cranial osteopathy is said to be based on a *primary respiratory mechanism*, a rhythm that can be felt with a very finely developed sense of touch. Some osteopaths believe that improving dysfunctional cranial rhythmic impulses enhances cerebral spinal fluid flow to peripheral nerves, thereby enhancing metabolic outflow and nutrition inflow. It has gained particular popularity in the treatment of babies and children.

Osteopathic manipulative medicine: The goal of Osteopathic manipulative medicine is the resolution of what many osteopaths call [somatic dysfunction](http://en.wikipedia.org/wiki/Somatic_dysfunction) in an attempt to aid the body's own recuperative faculties. Osteopathic manual treatment of the musculoskeletal system employs a diverse array of techniques. These are normally employed together with dietary, [postural](http://en.wikipedia.org/wiki/Human_position), and occupational advice, as well as counseling in an attempt to help patients recover from illness and injury, in an attempt to minimize or manage pain and disease.

Visceral osteopathy: Proponents of [visceral](http://en.wikipedia.org/wiki/Visceral) osteopathy state that the visceral systems (the internal organs: digestive tract, respiratory system, etc.) rely on the interconnection [synchronicity](http://en.wikipedia.org/wiki/Synchronicity) between the motion of all the organs and structures of the body, and that at optimal health this harmonious relationship remains stable despite the body's endless varieties of motion. The idea is that both *somato-visceral* and *viscero-somatic* connections exist, and manipulation of the somatic system can affect the visceral system (and vice-versa).Practitioners contend that visceral osteopathy relieves imbalances and restrictions in the interconnections between the motion of all the organs and structures of the body—namely, nerves, blood vessels, and fascial compartments. During the 1940s, osteopaths like H V Hoover and M D Young built on the work of Andrew Taylor Still to create this method of assessment and manipulation. The efficacy and basis of this treatment remains controversial even within the osteopathic profession.

Especially in children these techniques are well accepted because they are likely to cause no pain or other negative side effects. However, no evidence based data concerning safety and efficacy of osteopathic treatment in infants- especially in premature infants- are available so far.

Therefore, in the present study visceral osteopathic techniques are applied with the aim to accelerate meconium evacuation and establish proper gastrointestinal function in VLBW-infants . Furthermore the safety and efficacy of the applied osteopathic techniques should be surveyed.

**Materials and Methods:**

**Aim of the study:**

The aim of this prospective randomized trial is to determine whether early osteopathic treatment of bowel and colon has an influence on meconium evacuation in very low birth weight infants.

**Hypothesis:**

We hypothesize that a standardized treatment algorithm of osteopathic bowel techniques accelerates complete meconium evacuation in preterm infants.

**Patients and Inclusion criteria:**

Premature infants with a birth weight ≤1500 g and a gestational age (GA) ≤32 weeks are eligible for inclusion in the study.

**Exclusion criteria:**

Exclusion criteria were major congenital malformations and known gastrointestinal abnormalities.

**Design:**

The study design is performed as a prospective randomized controlled trial at the Neonatal Intensive Care Unit (NICU), Department of Pediatrics, Medical University of Vienna/Austria. Infants with a birthweight <1500g and a GA <32 weeks will be included, stratified according to their GA ( < 28 vs. ≥ 28 weeks) and assigned randomly to the intervention or control group. Randomization assignment is performed using sealed opaque envelopes that are grouped in an even blocked size design (block size 4) by stratification variable (GA).The study will be approved to the Ethics Committee of the Medical University of Vienna. Written informed consent will be obtained from the parents after full explanation of the procedure. Infants will be treated according the same standard care procedures for VLBW-infants used at our department.

Study groups:

Infants in intervention group will receive osteopathic treatment within their first 48 hours of life according the following protocol:

All techniques are applied in the supine position:

1. Global listening- any further treatment methods employed to improve mobility must be slow and gentle
2. Release lower ribs and thoracic diaphragm
3. Small intestine diagnosis- Lifting the gut and bringing it to a stillpoint
4. Root of mesentery diagnosis (and manipulation)
5. Mobilisation of the ileocoecalic valve
6. Mobilisation of colon ascendens, transversum, descendens
7. Root of sigmoid diagnosis and manipulation
8. As the 10th cranial nerve influences the intestines’ function by relaxing the sphincters and thus increases gut motility treatment of the parasypmatic nerval system should be always in involved

The treatment algorithm will be repeated three times during the first week of life.

No intervention is planned in the control group.

After admission of the patient to NICU, the infant received primary care according to

the standard principles of neonatal intensive care (monitoring of oxygen saturation,

heart rat, blood pressure, temperature, fluid intake and urine rate, intravenous access

by periphery or central venous line).

The nursing staff assesses the quality of stools as “meconium” (black, thick, sticky) or

“non meconium” by appearance and documented data into the “carevue”

documentation system.

The time to complete meconium evacuation is defined as day of life on which the last meconium was passed. Documentation of stool consistency, colour and amount will be continued until the end of the infants’ stay at the NICU. The observation period ends when the infant was transferred or discharged.

Data collection:

The following data will be recorded:

Before the first osteopathic treatment:

· Gestational age

· Birth weight

· Birth length

· Head circumference at birth

· APGAR

· Umbilical cord-PH

· Clinical condition of the abdomen (size, tension, peristaltic,

apparent standing intestinal loops)

· Stooling pattern

· Ventilation and ventilator support (PEEP)

For the whole duration of the study period, following data was recorded daily:

· Body weight

· Amount of parenteral fluids in ml/kg

· Enteral nutrition supply in ml/kg (Human milk or formula)

· Fortification of human milk

· Gastric residuals

· Stooling pattern

· Clinical condition of the abdomen (size, tension, peristaltic, apparent standing intestinal loops)

· Ventilation and ventilator support (PEEP and flow)

· Feeding intolerance

· Enemas

· Glycerin suppositories

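### A single, disclosed block size of 4 in a one-unit trial without described masking could let a recruiter who keeps count know about 30–33% of assignments in advance

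*Protocol*

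**What the plan says.** All of the relevant text is in the Protocol under Design. The trial is a "prospective randomized controlled trial at the Neonatal Intensive Care Unit (NICU), Department of Pediatrics, Medical University of Vienna/Austria", so there is one recruiting unit. Infants are "stratified according to their GA ( < 28 vs. ≥ 28 weeks) and assigned randomly to the intervention or control group". The mechanism is "sealed opaque envelopes that are grouped in an even blocked size design (block size 4) by stratification variable (GA". One block size is therefore fixed, and it is printed in the protocol.

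The same section describes the two arms. On the treated side, "The treatment algorithm will be repeated three times during the first week of life". On the other side, "No intervention is planned in the control group". No sham procedure and no masking of staff is described. Enrolment depends on the parents: "Written informed consent will be obtained from the parents after full explanation of the procedure". The primary outcome rests on a judgement made on the unit: "The nursing staff assesses the quality of stools as “meconium” (black, thick, sticky) or" not meconium.

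The total is 40 infants (Sample size), to be recruited over 4 to 6 months (Duration of the study). Cox models with birth weight and gestational age are planned (Statistical analysis).

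**The concern.** An opaque envelope hides the next card. It does not hide what follows from the cards already opened. When every block holds four places and the size is known, anyone who has seen the earlier assignments in a stratum can work out the fourth, and sometimes the third.

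Here the earlier assignments are likely to be visible, because some infants on the unit receive manual treatment and the others receive none. A person who can foresee the next assignment can affect whether or when a family is approached, and the arms may then differ in prognosis from the start.

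Two features make concealment worth protecting in this trial. The sample is small, so a few selectively enrolled infants could shift the baseline balance. And no masking is described for the nurses who grade the stools, so concealed allocation is one of the few protections against bias that the design can offer.

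**Working it through.** The protocol gives no figure for predictability, so there is none to reproduce. The calculation starts from the stated block size.

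**Inputs**
- Block size 4, one list per stratum, two strata (Protocol, Design).
- Total of 40 infants (Protocol, Sample size).
- Assumed: 1:1 allocation, so two places per arm in each block. The ratio is not stated; two arms and even blocks suggest it.
- Assumed: the recruiter sees earlier allocations, knows the block size, and counts separately in each stratum from its first infant.

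**Assignments known with certainty, complete blocks**

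A 2:2 block of 4 has C(4,2) = 6 equally likely sequences. An assignment is certain once one arm has used both its places.
- In 2 sequences (AABB, BBAA), positions 3 and 4 are certain.
- In the other 4, only position 4 is certain.

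Expected number per block = (2×2 + 4×1)/6 = 1.33 of 4, or 33.3%. By position, the probability of certainty is 0, 0, 1/3 and 1.

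**Over 40 infants**
- Both strata end on complete blocks: 10 blocks × 1.33 = 13.3 of 40 (33.3%).
- Strata end with 2 and 2 infants in unfinished blocks: 9 × 1.33 + 0 = 12.0 (30.0%).
- Strata end with 1 and 3 infants in unfinished blocks: 9 × 1.33 + 1/3 = 12.3 (30.8%).

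The protocol fixes no stratum sizes, so the range is 12 to 13 of 40.

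**Success rate of a best guess**

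The guesser names the arm with more places left and tosses a coin when they are equal. The success probabilities by position are 1/2, 2/3, 2/3 and 1. Their mean is (1/2 + 2/3 + 2/3 + 1)/4 = 17/24 = 70.8%, or 69.6% with unfinished blocks, against 50% by chance.

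**After a change of block sizes**

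The fixed-size rows are exact. The varying-size rows come from simulation: 4,000 runs, 20 infants in a stratum, sizes equally likely, and a guesser who knows the set of sizes but not their order. Simulating the fixed size of 4 in the same way gave 33.4% and 70.8%, in agreement with the exact values.

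| Block sizes | Certain | Best guess correct |
|---|---|---|
| 4, fixed | 33.3% | 70.8% |
| 6, fixed | 25.0% | 68.3% |
| 8, fixed | 20.0% | 66.6% |
| 2, 4, 6, varying | 3.8% | 69.5% |
| 4, 6, varying | 5.8% | 68.5% |
| 4, 6, 8, varying | 2.2% | 67.1% |

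With sizes 4 and 6, certain assignments fall from 13.3 to about 2.3 of 40 (0.058 × 40). Correct best guesses fall only from 28.3 (0.708 × 40) to about 27.4 (0.685 × 40).

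**Imbalance**

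The largest difference between arms at any point in a stratum is half the largest block: 4/2 = 2 now, 6/2 = 3 with sizes 4 and 6.

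**The case against.** The strongest reply is that the one-third figure is conditional. The recruiter must know the block size, see the earlier allocations, keep a count in each stratum and know where each block begins. Only the block size is documented. The protocol does not say who recruits, who holds the envelopes, or whether recruiters are present at treatment sessions. This stands: a reader might infer that the unit knows every past allocation, but that is an inference from an untreated comparator on one unit.

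The route to bias is also narrow. Eligibility rests on birth weight and gestational age, and treatment begins within 48 hours of birth, so there is little room to hold an infant back for a better envelope. Birth weight and gestational age, on which selection could most obviously act, are in the Cox models. This reduces the risk but does not remove it: a family can still not be approached, and the models cannot adjust for an unrecorded clinical impression.

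Stratified blocks of 4 with sealed opaque envelopes are a common design, and nothing in the section is miscalculated. That is true. The objection here is to the combination of one disclosed size, one unit and no described masking.

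Finally, a reader might take the 71% guessing rate as a harm that varying blocks would remove. They would not: the rate stays between 67% and 70% under the varying sizes examined. The gain lies in certainty.

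**Conclusion.** The point holds as a weakness in allocation concealment. Under 1:1 allocation, a recruiter who sees earlier allocations and counts by stratum could know 12 to 13 of 40 assignments (30–33%) for certain. The upper figure needs both strata to end on complete blocks.

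Two stronger readings are not supported. The documents do not show that anyone would use this knowledge, and no effect on the estimate or the type I error has been quantified, so it does not follow that the result would be biased. Nor is the protocol shown to be at fault for leaving out who prepares the list, how envelopes are numbered, or when they are opened relative to consent. Those are operational details that may sit in another document. What is evidenced is the fixed and disclosed block size, which is worth changing because the change is cheap.

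**What to change.** In the Protocol, Design, replace the fixed block size with randomly varying block sizes within each gestational-age stratum, for example 4 and 6. State only that the sizes vary, and keep the sizes themselves out of the protocol used on the unit.

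The cost is a new randomisation list, one revised sentence, and a maximum imbalance within a stratum of 3 instead of 2. Simply moving to a larger fixed size would do much less for certainty (25% with blocks of 6). Adding size 2 would lower certainty a little further (3.8% against 5.8%) but make guessing slightly easier (69.5% against 68.5%), so 4 and 6 is a reasonable choice.

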**Relevance for the patient:**

The potential benefit for the patient consists in shortened meconium passage, improved feeding tolerance, shorter time of parenteral nutrition and intravenous access and therefore lower sepsis morbidity and shorted hospital stay.

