**Secondary outcome:**

introduction of enteral feeding in days, feeding volume on day 14th

time to full enteral feeding in days,

**Statistical analysis** :

Given the non-normal distribution of the data, all comparisons will be performed using non-parametric tests. The Mann-Whitney U test will be used to detect treatment effects between the groups. Kaplan-Meier curves will be plotted to visualize differences in the time to complete meconium evacuation between the groups. Comparison of the curves will be performed using the log rank test. Multiple Cox regression models will be used to identify the possible influence of the covariates birth weight and GA. For all tests, a p-value < 0.05 was considered to indicate statistical significance. SPSS statistical software system (SPSS Inc., Chicago, IL, version 10.0) will be used for all calculations.

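### Observation ends at transfer or discharge, but two of the three secondary outcomes (day-14 feeding volume and time to full enteral feeding) can fall after that point

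*Protocol*

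**What the plan says.** The Design section of the protocol closes follow-up by location and not by age or event: "The observation period ends when the infant was transferred or discharged". Stool records follow the same limit: "Documentation of stool consistency, colour and amount will be continued until the end of the infants’ stay at the NICU". Enteral intake in ml/kg is among the daily items, introduced by "For the whole duration of the study period, following data was recorded daily". The study period is not defined separately from the observation period, and no collection from a receiving ward or hospital is described.

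The Secondary outcome section lists "introduction of enteral feeding in days, feeding volume on day 14th" and "time to full enteral feeding in days". That makes three outcomes, of which one is tied to a fixed day of life and one is an event with no upper time limit.

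Under Statistical analysis, "The Mann-Whitney U test will be used to detect treatment effects between the groups". The survival method is named for the primary outcome only: "Kaplan-Meier curves will be plotted to visualize differences in the time to complete meconium evacuation between the groups". The section on relevance for the patient lists as possible benefits "improved feeding tolerance, shorter time of parenteral nutrition and intravenous access and therefore lower sepsis morbidity and shorted hospital stay".

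**The concern.** A volume on day 14 needs every infant to be observed on day 14, and a time to full feeds needs follow-up until full feeds. A rule that stops observation whenever the infant moves guarantees neither. This is a rule about data collection, so the protocol has to settle it: an analysis plan can define censoring or missing-data handling, but it cannot recover a volume that nobody recorded.

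Two things are at stake. Fewer infants contribute to these outcomes in a trial of 40. More important, leaving the unit is a post-randomisation event. The protocol hopes that the treatment will improve feeding and shorten hospital stay. If that happens, and if leaving the unit is linked to feeding or stability, the treatment may change who still has a value to compare.

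**Working it through.** **Step 1: the collection window against what each secondary outcome needs.**

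| Secondary outcome | Observation needed | Assured by the protocol's window? |
|---|---|---|
| Introduction of enteral feeding | until the first feed | not shown to be at risk; not part of this point |
| Feeding volume on day 14 | the infant's intake on day 14 | no: absent if the infant leaves before day 14 |
| Time to full enteral feeding | until full feeds | no: unobserved if the infant leaves before full feeds |

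This step needs no figure. It follows from the wording.

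**Step 2: the protocol's own number.** The only design figure is 40 infants in total (20% difference, 80% power, significance level 0.05). It cannot be reproduced, because no SD, reference value or sidedness is given, and this point does not dispute it. Solved backwards, assuming 20 per arm and a two-sided test, it corresponds to a standardised difference of (1.960 + 0.842) × √(2/20) = 0.886.

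**Step 3: loss of precision, for assumed rates of early departure.** Power = Φ(0.886 × √(n/2) − 1.960), where n is the number per arm with a value. The 0.886 is borrowed from Step 2 as a yardstick, since the protocol makes no power statement for the secondary outcomes.

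| Assumed loss | n per arm | Power |
|---|---|---|
| 0% | 20 | 80.0% |
| 5% | 19 | 78.0% |
| 10% | 18 | 75.7% |
| 20% | 16 | 70.7% |
| 30% | 14 | 65.0% |

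**Step 4: possible bias in day-14 volume.** Every input here is an assumption: volumes are normal with SD 40 ml/kg, true means are 100 (control) and 120 (treated), and infants without a value are left out. Let c be a feeding threshold common to both arms and a = (c − mean)/40.

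*Best feeders leave.* If all infants above c leave, the mean of those remaining is mean − 40 × φ(a)/Φ(a). For the threshold exceeded by 10% of controls, c = 100 + 40 × 1.2816 = 151.3.
- Control: 100 − 40 × 0.1755/0.9000 = 92.2.
- Treated: a = 0.7816, so 120 − 40 × 0.2939/0.7828 = 105.0.
- Difference: 12.8 instead of 20.

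| Control threshold | Above it, control / treated | Difference if all of these leave | Difference if half leave |
|---|---|---|---|
| nobody leaves | 0% / 0% | 20 | 20 |
| top 2% | 2% / 6% | 16.9 | 18.5 |
| top 10% | 10% / 22% | 12.8 | 17.1 |
| top 20% | 20% / 37% | 10.2 | 17.0 |

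*Poorest feeders leave.* If all infants below c leave, the mean of those remaining is mean + 40 × φ(a)/(1 − Φ(a)). For the lowest 10% of controls, c = 48.7.
- Control: 100 + 40 × 0.1755/0.9000 = 107.8.
- Treated: a = −1.7816, so 120 + 40 × 0.0816/0.9626 = 123.4, with 4% missing.
- Difference: 15.6. With a common threshold, this route shrinks the difference too.

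*The pattern differs between arms.* The difference can then move either way. If only the treated arm loses its poorest 10%, the treated mean becomes 120 + 7.8 = 127.8 and the difference is 27.8. If only the treated arm loses its best 10%, it is 120 − 7.8 − 100 = 12.2.

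These are differences in means, whereas the planned test compares ranks, so they show direction and rough scale only.

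**The case against.** The strongest reply is that the text shows a gap but not harm. The infants weigh at most 1500 g at birth and include a stratum below 28 weeks. Nothing in the protocol suggests that many leave within 14 days, and it gives no transfer rate. If none leave early, nothing is lost. This stands, and it is why the range starts at nil. It is weaker for time to full feeds, which has no upper limit.

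The possible bias in time to full feeds also depends on why infants leave. Those who leave because feeding goes well are likely to have reached full feeds already, so under that mechanism this outcome loses little. That also stands. The outcome is exposed mainly when infants move for other reasons.

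Three stronger readings are tempting, and the documents support none of them:

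- A reader might infer that early leavers are excluded from the comparisons. The protocol does not say so. The Mann-Whitney test needs a value for each infant and the survival curves are named only for meconium evacuation, but the Cox models are not tied to one outcome, and an analysis plan not shown could set a censoring or missing-data rule.
- A reader might infer that a real benefit would be understated. The protocol does not say that leaving the unit depends on feeding; it only lists a shorter hospital stay among possible benefits. The direction cannot be determined from it.
- A reader might infer that all the feeding outcomes are compromised. Introduction of enteral feeding is not shown to be affected.

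**Conclusion.** The point holds as a gap in data collection affecting two of the three secondary outcomes. Followed as written, the protocol yields no day-14 volume for an infant who leaves before day 14, and no observed full-feeds date for one who leaves before full feeds. No later analysis plan could recover those values.

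Bias is conditional. It requires early departures, and it requires that leaving be related to feeding or stability; both are assumptions. Its size runs from nil upward. Under the assumed volumes it takes 1.5 to 9.8 ml/kg off a true difference of 20 when infants above a common threshold leave early (20 − 18.5 and 20 − 10.2). It can go in either direction if the pattern of leaving differs between arms. Because the outcomes are secondary and the frequency is unknown, this is a worthwhile inexpensive correction and not a threat to the trial's main conclusion.

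**What to change.** Amend the observation-period paragraph of the Design section so that the feeding data for these two outcomes are collected until day 14 or the day full enteral feeding is reached, whichever is later, wherever the infant is. For an infant who has moved, take the day-14 volume and the date of full feeds from the receiving ward's or hospital's chart.

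Where the full-feeds date cannot be obtained, analyse that outcome by Kaplan-Meier and log rank, the methods already planned for the primary outcome, with censoring at last contact. This is only a fallback. It keeps the infant in the analysis, but if leaving is related to feeding the censoring is informative and the bias remains. Retrieving the chart values is what addresses the problem.

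The cost is at most two routine chart values for each infant who leaves before reaching them, with no extra procedure and no change in care. The downside is a few chart requests and consent wording that covers the receiving hospital's records, so the change is best made before enrolment starts.
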